##### Patient Participants

We will exclude pregnant women, neonates, and infants aged 0-23 months owing to the known teratogenic effects of radiation in this population, as trauma evaluation in this study will involve obtaining radiographs for orthopedic injuries and CT scans for neurological injuries. Patients with documented stroke will also be excluded, as the study outcomes involve assessment for functional, physical, and neurological disabilities directly attributable to trauma. Moreover, mentally incapacitated patients who have no legally authorized representatives to sign an informed consent form and patients who die before hospital arrival or before imaging results are obtained will be excluded. Patients who are passengers in a car or drivers in a car at the time of the accident will be excluded, as the protective casing of the car body would make these patients less vulnerable to direct impacts compared with pedestrians, cyclists, or passengers on motorcycles. In addition, elderly patients older than 80 years will be excluded owing to their increased risk of fragility fractures that could misrepresent the severity of trauma. This cutoff age was used based on a systematic review by Tsuda et al [24], which documented a mean age of 80 years for long bone fragility fractures owing to increased muscle weakness, balance disorders, visual impairment, and dementia that predispose elderly people to falls. The number of ineligible participants and the reasons for their exclusion will be recorded in both arms in the consolidated standards of reporting trials flow diagram.

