### Outcomes

This trial will examine both process measures and patient outcomes. The primary (process) outcomes of this trial will involve comparisons of (1) the time interval from the accident to hospital admission and (2) the time interval from the referral decision to hospital discharge between patients with motorcycle accident–related injuries presenting to the intervention centers and those presenting to the control centers.

The secondary (patient) outcomes of this trial will involve comparisons of (1) all-cause mortality at 90 days from the time of injury and (2) morbidity of motorcycle accident–related orthopedic and neurological injuries between patients presenting to the intervention centers and those presenting to the control centers. The morbidity of orthopedic injuries will be measured based on the Trauma Expectation Factor Score (TEFS) at admission and the Trauma Outcome Measure Score (TOMS) at 90 days as reported to outcome assessors [28]. On the other hand, for neurological injuries, the Glasgow Coma Scale (GCS) at admission and Glasgow Outcome Scale (GOS) at 90 days will be used as documented by the attending clinicians [29].

The tertiary outcomes will involve the effects of the training on provider knowledge based on pretraining and posttraining trauma-related MCQ scores and the barriers to injury care faced by providers during execution of definitive treatment. These will be determined in 2 ancillary studies that have been approved as part of this trial, and the protocols have been detailed elsewhere [25]. A summary of all outcomes and their case definitions, specific measurement variables, analysis metrics, methods of aggregation, and time points has been provided in Multimedia Appendix 3.

The patient outcomes were selected based on their validity and relevance in previous studies [7,30]. Further, level III evidence suggests that prolonged prehospital times may be associated with increased mortality among trauma patients [31]. However, it is unclear how these results relate to time-sensitive orthopedic and neurological injuries in LMICs that lack formal coordinated prehospital systems [32]. Thus, our process outcome measure variables were selected within the context of evidence-based practice. This practice stipulates that in accordance with the golden hour rule, a major trauma patient should be in the right place within 60 minutes following injury, otherwise there is a risk of mortality or morbidity [33].

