### Participant Timeline

Initially, cluster randomization of the trauma centers will be performed 3 weeks prior to commencement of the training to determine which centers will receive the training. Potential participants for the training will be screened for eligibility by the hospital and study administrators 2 weeks prior to the training, and eligible trainee participants will be consented and assigned to “rural trauma teams” of 6 members on the first day of the training, during which they will complete a pretraining questionnaire involving trauma-based MCQs. Subsequently, trainee participants will be followed up at 90 days (3 months) to complete posttraining MCQs. The first eligible patient participants at both control and intervention sites will be enrolled concurrently through a motorcycle trauma outcome registry (MOTOR) that will run parallel to the trial.

Informed consent, baseline sociodemographic and clinical characteristics, and prehospital intervals will be obtained at admission, and the GCS score will be determined. The TEFS will be obtained during the first week of admission or prior to discharge on the assumption that patients would have received their definitive surgical intervention or would have been referred for further care during this period. Further, the GOS score, all-cause mortality rate, and TOMS will be obtained at the 90-day follow-up. The GCS will be used to assess the level of traumatic brain injury in the acute phase, whereas the GOS will be used to determine neurological outcomes within the context of the level of independence at a later phase of traumatic brain injury [29]. On the other hand, the TOMS will be used to assess patient-reported trauma outcomes with reference to their expectations (TEFS) at the time of the trauma intervention in relation to the levels of pain, physical function, disability, injury treatment satisfaction, and overall satisfaction [28,30]. Throughout the study period, any individual patient barriers encountered during the pathway to execution of definitive injury care will be documented as summarized in the timeline presented in Multimedia Appendix 4.

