### Data Collection and Management

#### Plans for Assessment and Collection of Outcomes

Data collection will start simultaneously at all the study sites. Medical officers (blinded outcome assessors) with a minimum qualification of Bachelor of Medicine and Bachelor of Surgery (MBChB) and at least 2 years of clinical experience will prospectively collect data through clinical observations, interviews, home visits, and extraction from hospital and police records. All outcome assessors must be willing to undertake a 1-day budgeted training in the use of data collection tools for this trial and the World Health Organization (WHO) ICD-10 online coding module. The data will be collected daily as medical trainees and interns will attend clinical rotations every day. Upon obtaining informed consent, the venue for data collection, including follow-up information, will be at accident and emergence departments during admission, surgical wards, and outpatient clinics, as well as through home visits and phone calls to patients, care takers, or recipient hospital physicians in the case of referrals.

The study variables will include sociodemographic and clinical variables, such as sex, age, injury mechanisms, including nature of collision and road user category, time of injury, prehospital transit time, prehospital care, mode of arrival, vital signs, nature of physical injuries, radiological findings, and injury severity based on the GCS score and Kampala Trauma Score (KTS) [43]. In addition, data on the nature of the treatment administered; need for referral; referral-exit interval; and outcomes, including the TOMS, GOS score, mortality, and time from injury to death, will be obtained. The data collection tools that will be used in this trial, such as the GCS, GOS, TEFS, TOMS, and KTS, have been shown to demonstrate excellent criterion internal validity, consistence, and reproducibility in previous studies [28,29,43,44].

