For all-cause mortality, the difference in proportions of all deaths at 90 days after injury will be compared between the intervention and control groups using the chi-square test if the expected count is >5 or the Fisher exact test at 95% CI otherwise. Lastly, we will conduct subgroup analyses to determine and control for factors associated with all-cause mortality using individual- and cluster-level between-within mixed effects regression models. The covariates will include age, sex, injury mechanism (including helmet use), mode of arrival, prehospital interval, referral decision to hospital discharge interval (dichotomized as ≤1 hour or >1 hour), prehospital first aid status, comorbidities, injury severity score based on the GCS at baseline, multiplicity of injuries, head and brain CT-based diagnosis, and neurosurgical intervention.

These variables have been found to influence outcomes following neurological trauma in previous studies [7]. All variables will be analyzed for confounding and effect modification using Mantel-Haenszel statistics to probe necessary interaction terms. Variables with *P* values of ≤0.2 in the bivariate analysis will be included in the multivariate analysis. The median (IQR) of the time to the event, that is, from the accident to death (in days), will be stratified by treatment arm, and the difference will be compared using the Wilcoxon 2-sample test. All analyses will be performed using Stata 15.0, and where appropriate, graphics, such as box plots, will be used to visualize the data.

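### As written, the Wilcoxon test on days from accident to death can use only patients who died, so its direction depends on which deaths the training prevents, not on whether it prevents deaths

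*Protocol article*

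**What the plan says.** The Outcomes section of the protocol article lists "all-cause mortality at 90 days from the time of injury" as a secondary outcome, together with orthopedic and neurological morbidity. Time to death is not on that list, although the data collection section says that "outcomes, including the TOMS, GOS score, mortality, and time from injury to death, will be obtained".

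The section Secondary (Patient) Outcomes contains two separate comparisons of deaths:

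- For deaths by day 90, "the difference in proportions of all deaths at 90 days after injury will be compared between the intervention and control groups", by a chi-square test, or by the Fisher exact test when expected counts are small. Mixed effects models for factors associated with mortality follow.
- For timing, the median and IQR of the time "from the accident to death (in days), will be stratified by treatment arm, and the difference will be compared using the Wilcoxon 2-sample test".

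The second comparison comes with no censoring rule, no Kaplan-Meier curve, no log-rank or Cox analysis, and no rank assigned to patients who are alive at day 90.

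**The concern.** A patient who survives has no accident-to-death time. A median, an IQR and a two-sample Wilcoxon test on that variable therefore use the deaths alone. Dying is something the trial expects the training might change, so the two groups of dead patients are not the groups that randomization made comparable.

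What the test picks up is a difference in the mix of early and late deaths. If training saves patients who would have died late, the remaining deaths are mostly early, the median falls, and the result reads as if training hastens death. If it saves patients who would have died early, the median rises. If it saves both in proportion, the test has nothing to find however many lives are saved.

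At stake is a P value about deaths that may contradict the mortality result printed beside it.

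**Working it through.** **What the documents supply.** They state no figure for time to death. The number per arm can be reproduced from the Sample Size section: 10 × 12 × 3 × 2 = 720; 720 × (1 + 9 × 0.02) = 849.6, given as 850; 850 × 1.18 = 1003; 1003 / 2 = 501.5, given as 502 per arm. Follow-up is 90 days. A two-sided 5% level is assumed. Mortality and the distribution of death times are not given, so everything below is an assumed range.

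**Small example.** Assume 60 control deaths: 30 early (exponential, mean 2 days) and 30 late (day 5 plus exponential, mean 15, so 20 days on average).

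- *Half of the late deaths prevented.* 30 + 15 = 45 deaths, 25% fewer. The middle death is at about 22.5 / 30 = 75% of the early group: 2 × ln 4 = 2.8 days. Simulation (4000 runs) gives average medians of 2.80 days against 5.93 in control, with P < .05 in 16.6% of runs.
- *Half of the early deaths prevented.* 15 + 30 = 45 deaths. The middle death is about (22.5 − 15) / 30 = 25% into the late group: 5 + 15 × ln(1 / 0.75) = 9.3 days. Simulation gives 9.6 days against 5.9, significant in about 15% of runs.

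The number of lives saved is the same in both cases, and the sign is opposite.

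**At the planned size.** 502 per arm, 2000 runs per row, clustering ignored. Half of control deaths fall uniformly on days 0–7 and half on days 7–90, rounded up to whole days. The Wilcoxon test is applied to those who died, and a chi-square test for 90-day mortality to all patients.

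| Control mortality | Deaths prevented | Mean deaths, training vs control | Average median days | Wilcoxon P < .05, earlier with training | Wilcoxon P < .05, later with training | Mortality P < .05 |
|---|---|---|---|---|---|---|
| 5% | half of late | 18.8 vs 25.2 | 6.6 vs 13.6 | 14.6% | 0.3% | 16.3% |
| 10% | half of late | 37.5 vs 50.2 | 5.8 vs 11.5 | 24.9% | 0% | 29.3% |
| 20% | half of late | 75.4 vs 100.3 | 5.8 vs 10.4 | 47.5% | 0% | 54.1% |
| 5% | half of early | 19.0 vs 25.2 | 28.5 vs 13.4 | 0.1% | 15.6% | 15.1% |
| 10% | half of early | 37.8 vs 50.6 | 28.5 vs 11.6 | 0% | 25.4% | 29.5% |
| 20% | half of early | 75.3 vs 100.7 | 28.2 vs 10.3 | 0% | 47.8% | 56.3% |
| 10% | half of both | 25.1 vs 49.9 | 13.3 vs 11.9 | 2.3% | 2.5% | 84.8% |
| 10% | none | 50.1 vs 50.2 | 11.7 vs 11.5 | 2.6% | 2.4% | 5.7% |

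If three quarters of the late deaths are prevented, the test is significant for earlier death with training in about 34%, 64% and 92% of trials at 5%, 10% and 20% mortality. If both kinds are halved, the result at 5% and 20% mortality is like that at 10%: about 4% to 5% significant in total.

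At 10% mortality the test uses about 100 of the 1003 patients (0.10 × 1003).

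**The case against.** **The wording does not say that only the dead are compared.** That is correct. It speaks of time to the event and of a two-sample Wilcoxon test, whereas the primary outcome section names the rank sum test. A Wilcoxon test for censored data exists, and an appendix or analysis plan that is not shown could specify it. But the variable is defined as ending in death, no censoring is mentioned, and an all-patient median does not exist if fewer than half of the patients die. The decedent reading is the workable one, so the point is made about the text as written.

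**The consequence is small.** This largely stands. Mortality is compared in all patients in the same section, and time to death is not a listed secondary outcome and has no power claim or decision rule. A reader might infer that the trial lacks a comparison of survival that includes everyone, or that its mortality conclusion is invalidated by this line. The documents do not support that.

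**The direction is not fixed.** This stands too. A reader might infer that the test is biased towards harm. The early-death rows show the reverse, and the golden hour rationale in the Outcomes section points at least as much to early deaths as to late ones. In the half-of-late scenarios most simulated trials show no significant difference.

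**It is only descriptive.** It is not: a between-arm test is specified. Nor does the plan to impute missing end points help, because a survivor's death time is not missing but undefined.

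Two further matters are not counted here. Ignoring hospital clustering affects the other two-sample tests as well, so it is not particular to this line. The rule that "patients who die before hospital arrival or before imaging results are obtained will be excluded" could shift early deaths between arms if training speeds arrival, but it bears on every mortality analysis and cannot be sized from the documents.

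**Conclusion.** The concern holds for the test as written. It compares groups defined by an outcome of the trial, so its P value does not measure an effect on survival. It can point to earlier death, to later death or to nothing while deaths fall. Under the assumed scenarios a misleading significant result for earlier death occurs in about 15% to 47% of trials when half of the late deaths are prevented, against about 2.5% by chance.

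These percentages rest on assumed mortality of 5% to 20%, an assumed even split of early and late deaths, and independent patients. The dependence on the mix of early and late deaths does not rest on those values.

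The weight is modest: this is a supplementary comparison beside a mortality analysis in all patients. It should be changed because the change is cheap and the conflicting P value is avoidable.

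**What to change.** The minimum change is to drop the Wilcoxon P value and report the median and IQR of days to death among those who died, by arm, as description only, with the number of deaths and a note that the arms are not comparable on this measure.

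If survival time is to be compared, include all patients from accident to death, censored at day 90, or at last contact where that date is recorded. Show Kaplan-Meier curves by arm and use a comparison that respects the six hospitals. One choice is 90-day restricted mean survival for each hospital, compared by a t test on six values with 6 − 2 = 4 df. Another is a Cox model with hospital frailty, but only with a small-sample correction, since there are three hospitals per arm.

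The cost is a little more analysis. The article shows that time from injury to death is collected. It does not show that a last-contact date is, so for patients lost to follow-up that date would have to be recorded or recovered from the follow-up calls and visits.

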#### Interim Analyses

The Uganda National Council for Science and Technology accessed a preliminary report of the interim analysis, which was performed on August 28, 2022, when half of the sample size (n=500) was attained, and at its discretion, it recommended continuation of the study. The requisite characteristics for early termination set by the ethics committee included the occurrence of an index patient-reported adverse outcome definitely attributable to the study in accordance with the framework described by Okoniewska et al [48].

#### Methods for Additional Analyses

Subgroup analyses will be performed for (1) varying road user categories (pedestrian, passenger, and motorcyclist); (2) injury mechanisms (motorcycle-motorcycle accident, motorcycle-pedestrian accident, motorcycle-static object accident, and motorcycle-car accident); (3) varying injury severities (mild, moderate, or severe based on the KTS and GCS); and (4) multiplicity of serious injuries (one or multiple). To determine the training-effect heterogeneity across time periods, we will use an extension of Hussey and Hughes fixed effects model [49] for determining whether the intervention effect differs for each training period as summarized in the schematic representation of the study design (Multimedia Appendix 7).

For the ancillary study on provider outcomes, the difference in pretraining and posttraining mean scores will be computed with 95% CIs if the data are normally distributed; otherwise, the difference in median and IQR will be reported. For the qualitative ancillary study on the perceived barriers to injury care, directed content analysis of themes of transcribed data will be collated manually and presented as percentages.

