Research has shown than more than half of the trauma patients in Uganda do not receive first aid prior to hospital arrival [6,7]. Moreover, most of these patients arrive at dedicated trauma centers much later than the recommended limit of 1 hour, and they are transported by either public vehicles, such as motorcycles [8], or police vans, without any focus on key factors, such as changes in blood pressure and oxygen circulation, which could lead to death, during transit [7,14]. These aspects have 3 important implications. First, strengthening the capacity for injury care among lay frontline workers. Second, stabilizing patients at rural regional trauma centers prior to transfer. Third, ensuring closed-loop communication between primary (level 3) and tertiary (level 1) trauma centers to enable safely coordinated referrals and adequate preparation at the receiving hospitals prior to patient transfer.

The key challenge that needs to be addressed in Ugandan rural settings is the lack of a formal prehospital care system as evidenced by emergency evacuation and transfer of trauma patients by untrained police staff [14]. Further, there is an immense need to redress the weak immediate care response after an accident as medical trainees are the first point of contact after an accident as opposed to specialists [12]. We will attempt to fix these challenges at the community level and at level 3 rural trauma centers by creating and providing training capacity for rural trauma networks between traffic police and medical interns or trainees at regional referral hospitals.

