##### Trainee Participants

We will include third-year or fifth-year medical or allied health students, interns, or specialty residents in surgery and traumatology clinical rotations who stay at the hospital of attachment for at least 2 months. Medical students may only rotate to a different hospital without crossing the study arm. In addition, we will include road traffic law enforcement professionals concerned with the evacuation of trauma patients from accident scenes.

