To enable an active “alarm” activation criterion for the trauma committees, closed-loop communication, and a smooth “handover” process from police officers to medical trainees prior to patient transfer, the trained traffic officers on highways will serve as focal contact persons for the rural trauma teams from the parish (subcounty) level. In the event of a road traffic accident, teammates will freely contact each other both within and across teams to coordinate evacuation, consultation, referral, and arrival at recipient centers, with the support of trained interns and surgery residents as team leaders. Weekly audit meetings will be conducted remotely via Zoom (Zoom Video Communications) to discuss team challenges, otherwise a trained surgery resident will be available 24/7 to advise on referrals, transfers, and treatments in liaison with consultants who may be physically or remotely available. The control hospitals in this trial will be allowed to provide routine standard care without the RTTDC intervention as summarized in Figure 1.

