Further, the tools are recognized for their high interrater reliability, sensitivity to change, and ability to be used as continuous or categorical variables in validation studies [28,29,43,44]. The baseline TEFS, GCS score, and KTS will be added as covariates whose interaction and confounding will be assessed and controlled since the inclusion of baseline values of outcomes as covariates is arguably one of the strongest factors to reduce ICC estimates [45]. The difference in distribution of baseline characteristics will be compared using means (SDs), medians (IQRs), and ranges for quantitative data; otherwise, frequencies and percentages will be used for categorical variables. All data collection forms for this trial and detailed definitions of assessment tools for patient and trainee participants are available in Multimedia Appendix 5 and Multimedia Appendix 6, respectively.

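### Severity subgroups rest on KTS and GCS recorded after the trained network can act, so patients can shift between strata by arm and within-stratum effects can be biased in either direction

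*Protocol article*

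**What the plan says.** Under Methods for Additional Analyses the protocol article lists four subgroup factors: road user category, collision type, multiplicity of serious injuries, and "varying injury severities (mild, moderate, or severe based on the KTS and GCS". The Methods paragraph of the Abstract gives the purpose of the subgroup analyses: to evaluate and control confounding by injury mechanism and severity.

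The timing of the scores comes from three places:

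- Outcomes: "the Glasgow Coma Scale (GCS) at admission".
- Participant Timeline: baseline clinical characteristics are gathered when the patient is admitted, and "prehospital intervals will be obtained at admission, and the GCS score will be determined".
- Plans for Assessment and Collection of Outcomes: "The baseline TEFS, GCS score, and KTS will be added as covariates whose interaction and confounding will be assessed and controlled".

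Admission timing is thus explicit for GCS. For KTS it follows from the word baseline.

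The intervention can act earlier:

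- Participant Timeline: hospitals are randomised three weeks before training starts.
- Trainee Participants: those trained include "road traffic law enforcement professionals concerned with the evacuation of trauma patients from accident scenes".
- Intervention Description: "teammates will freely contact each other both within and across teams to coordinate evacuation, consultation, referral, and arrival at recipient centers".
- Background: one stated weakness of current transport is the lack of attention to "changes in blood pressure and oxygen circulation, which could lead to death, during transit".
- Outcomes: the first primary outcome is the interval from accident to admission, which lies entirely before the scores are taken.

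**The concern.** Grouping patients by admission severity is safe when allocation follows admission. Here allocation comes first, and the intervention is designed to act between the crash and the emergency department. If training changes a patient's condition or time of arrival, it can change the stratum in which that patient is recorded. A patient scored severe at a control hospital might have been scored moderate at an intervention hospital. The stratum called moderate then holds different kinds of patient in the two arms, and comparing deaths within it is no longer a randomised comparison.

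A false pattern by severity could then be read as effect modification, or as absence of benefit in particular groups, in a trial meant to inform scale-up. Treating the stratification as control of confounding makes this worse, because conditioning on a variable that the intervention may change can create bias. The regression models that adjust for baseline GCS or KTS share the weakness.

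**Working it through.** **Document inputs.** No stated figure is in dispute. The arm size used below is the protocol's own and reproduces: 10 × 12 × 3 = 360 per arm; 720 × (1 + 9 × 0.02) = 849.6, about 850; 850 × 1.18 = 1003; half is about 502. The document gives no mortality rate and no severity mix, so everything else is assumed.

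**Check 1: moving patients with every death held fixed.** Assume mild/moderate/severe shares of 60/25/15% and mortality of 1/8/35%. Overall mortality is 0.006 + 0.020 + 0.0525 = 7.85% in both arms. In the training arm let 20% of severe patients be recorded as moderate and 20% of moderate as mild, each keeping the risk of the stratum left.

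- Severe: share 0.12, deaths 0.042, mortality 35%; OR 1.00.
- Moderate: share 0.25 − 0.05 + 0.03 = 0.23; deaths 0.020 − 0.004 + 0.0105 = 0.0265; mortality 11.5%; OR = (0.0265/0.2035)/(0.08/0.92) = 1.50.
- Mild: share 0.65; deaths 0.006 + 0.004 = 0.010; mortality 1.54%; OR = (0.010/0.640)/(0.01/0.99) = 1.55.
- Overall: 0.010 + 0.0265 + 0.042 = 7.85%, unchanged.

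The Mantel-Haenszel OR is 1.22. Exchanging the arms, so that the training arm is the one scored worse, gives the reciprocals: 1/1.55 = 0.65, 1/1.50 = 0.67, 1.00, and 1/1.22 = 0.82. With no shift every OR is 1.00.

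Two further mixes were tried (70/20/10% with mortality 1/5/25%; 50/30/20% with 2/10/45%), and shifted patients were given 0.25 to 1.0 of their stratum's risk:

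| Share shifted down | Mantel-Haenszel OR, no death changed |
|---|---|
| 5% | 1.04–1.06 |
| 10% | 1.08–1.12 |
| 20% | 1.18–1.28 |
| 30% | 1.28–1.49 |

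**Check 2: a latent severity model.** Crash severity S ~ N(0,1). Arrival score A = 0.8S + 0.6e − d × arm, with e ~ N(0,1) and d the improvement in SD. Logit P(death) = −3.0 + 1.3S + b × arm. Strata are cut at the 60th and 85th control percentiles of A. Mortality in a stratum is ∫P(death|S)·P(A in stratum|S)φ(S)dS divided by ∫P(A in stratum|S)φ(S)dS, evaluated numerically. Control mortality is 8.5%.

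| d | Severe share, training arm | Stratum ORs, b = 0 | Stratum ORs, b = −0.3 (overall OR 0.77) |
|---|---|---|---|
| 0 | 15.0% | 1.00 | 0.75–0.77 |
| 0.1 | 12.8% | 1.07–1.10 | 0.80–0.83 |
| 0.2 | 10.8% | 1.14–1.20 | 0.85–0.91 |
| 0.3 | 9.1% | 1.21–1.32 | 0.91–1.00 |

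Reversing the sign (arrival scores worse under training, b = 0) gives 0.91–0.93, 0.83–0.87 and 0.76–0.81 for shifts of 0.1, 0.2 and 0.3 SD. The overall OR is 1.00 in every b = 0 row.

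**Check 3: bias against sampling error.** At d = 0.2 and 502 per arm the severe stratum holds 502 × 0.15 = 75 control and 502 × 0.108 = 54 training patients. Control mortality there is 23.3%, so expected deaths are about 17.5 and, at OR 1.155, about 14.1. SE(log OR) = √(1/17.5 + 1/57.8 + 1/14.1 + 1/40.2) = 0.41. The 95% interval around 1.16 is about 0.51 to 2.59, before any allowance for clustering.

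**The case against.** The strongest reply is that the shift is assumed. Nothing in the document shows that training alters arrival physiology, and the prehospital route is partial. The planned trainees are 66 police officers against 12 + 30 + 140 + 264 = 446 residents, interns and students, and patients may also come by ambulance or public transport. This stands: patients can shift, but the document does not show that they will.

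A reader might infer that the bias usually runs against the training, and that it could show harm in every severity group while overall mortality improves. The document supports neither. Patients who die before arrival or before imaging are excluded, so faster evacuation could bring sicker patients into the training arm and reverse the sign. With a true OR of 0.77, no stratum in Check 2 rises above 1. Benefit is masked, and harm does not appear.

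The bias is also modest beside the noise (Check 3). Ignoring clustering, the latent model puts false-positive rates per stratum at about 6–8% for a 0.2 SD shift and 7.5–10% for 0.3 SD. The reallocation model is harsher: 15% in the moderate stratum at a 20% shift in the central case. For the first primary outcome (difference 1.02 h, SD 1.64 h), a 0.3 SD shift with an assumed severity–time correlation of 0 to 0.2 leaves within-stratum differences of 0.95–1.02 h. The problem is therefore mainly one for mortality, a secondary outcome.

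Finally, these are additional analyses, and a separate analysis plan may label them. That limits the reach but does not remove the point: the article itself fixes the variable, the timing of GCS and the confounding-control purpose.

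**Conclusion.** The point holds as a conditional one. The severity strata use scores taken after allocation and after the trained network can act: explicit for GCS, inferred for KTS. They can therefore differ in make-up by arm, and within-stratum mortality effects can be biased either way with no death changed. Under the assumed latent model, shifts of 0.1 to 0.3 SD give null odds ratios of about 1.07 to 1.3 if arrival scores improve, and about 0.93 down to 0.76 if they worsen. With no shift there is no bias. Severity mix, mortality, correlation and shift are all assumptions, and the true shift cannot be learned from the document. Unadjusted overall comparisons are unaffected by stratum migration, and so are the subgroups by road user and collision type. The repair is worth making because it is nearly free and guards against a false effect-modification claim.

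**What to change.** In Methods for Additional Analyses:

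- Label the KTS and GCS strata descriptive, and state that no conclusion on effect modification or control of confounding will be drawn from them.
- Report arrival KTS and GCS by arm as possible intermediate outcomes, so that readers can see whether a shift occurred.
- Rest effect-modification claims on factors the intervention cannot move: road user category and collision type.
- Use multiplicity of serious injuries, already a listed subgroup, as the less movable severity proxy, with the caveat that it too is ascertained after arrival.

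Strata built on imaging findings are not a clean substitute. Imaging is requested after arrival by the cadres being trained, and deaths before results are excluded.

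The cost is wording and one table, with no new data. The trial gives up a formal effect-modification claim by arrival physiology, and injury multiplicity may separate prognosis less sharply.
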